**Methods/Design:**

Contact&Connect will use a parallel individual randomized design to evaluate the effectiveness of a multimedia-based intervention aimed at reducing stigma. The intervention consists of a package of 12 brief contact interventions (BCIs) delivered over a six month period. BCIs will direct participants to informational programs and microsites. Content will address three major themes: debunking depression myths and stereotypes, normalisation, and empowerment. Target enrolment is 630 (315 in each arm), each to be followed for 12 months. Eligible participants will be males, between 30 and 64 years, unemployed at the time of recruitment, registered with Incolink (a social welfare trustee company for unemployed members of the construction industry), and own a smart phone with enabled internet connectivity.

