## Methods

### Study design

Contact&Connect is an individual-level two-arm randomised controlled trial (Additioanl File 1). A total of 630 participants (315 in each arm) will be recruited. Simple randomisation using a random numbers table generated by computerised software (Stata for Windows, version 13 [13]) will be used to establish the randomisation sequence. Participants will be allocated to either the intervention or wait-list control group by an offsite researcher working independently from the research team. Owing to the nature of this intervention, neither the participants themselves nor the intervention team will be blind to allocation. However, outcome assessors will remain blind to treatment allocation through the use of unique study identifiers.

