### Same size and power calculations

Assuming, in line with previous work on interventions to improve mental health literacy in other occupational groups [21], a difference of 0.73 in beliefs about depression treatment between the intervention and control groups at post-intervention, a minimum of 226 participants per group will be required to detect this difference at the nominal 0.05 significance level with 90 % power. For our secondary outcomes, our previous study has shown that 13 % of the working population report suicide ideation [22]. We believe it is realistic to expect a change from 13 % to 8 % prevalence following the trial. Power calculations indicate we will need 267 persons per group to detect this difference at the nominal 0.05 significance level with 80 % power. Assuming 30 % drop-out, we therefore aim to recruit a total of 630 newly unemployed participants over a three month period. This is a feasible and achievable goal, given that approximately 20 unemployed workers lodge a claim each day with Incolink. We will recruit over a period of three months, thus allowing us to obtain a sample size adequately powered to assess both primary and secondary outcomes.

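### With the plan's own 30% drop-out, 630 recruits leave about 220 per arm: well short of the 267 required for suicidal ideation and just short of the 226 required for the primary outcome

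*Protocol article*

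**What the plan says.** All the inputs stand in one paragraph of the protocol article, under Same size and power calculations.

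- Primary outcome: the assumed effect is "a difference of 0.73 in beliefs about depression treatment between the intervention and control groups at post-intervention", for which "a minimum of 226 participants per group will be required to detect this difference at the nominal 0.05 significance level with 90 % power". No standard deviation is given.
- Secondary outcome: for a fall in suicidal ideation from 13% to 8%, "we will need 267 persons per group to detect this difference at the nominal 0.05 significance level with 80 % power".
- Attrition and target: "Assuming 30 % drop-out", then "we therefore aim to recruit a total of 630 newly unemployed participants over a three month period".

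The paragraph closes by saying that this sample has adequate power for the primary and the secondary outcomes alike. The Study design section fixes the split: "A total of 630 participants (315 in each arm) will be recruited". The abstract repeats it: "Target enrolment is 630 (315 in each arm), each to be followed for 12 months". No section gives another drop-out rate or confines the allowance to one outcome.

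**The concern.** The paragraph presents 630 as the result of the two per-group requirements and the drop-out allowance. If that were so, removing 30% from 315 should leave at least 267 per arm, the larger requirement, because the paragraph claims adequacy for both outcomes. It leaves fewer than either requirement.

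What is at stake is mainly how the suicidal ideation result will be read. The plan chose to power that outcome and says that it has done so. A null result would be taken to come from an adequately powered comparison when, under the trial's own attrition assumption, it would not have.

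**Working it through.** **Inputs** (Same size and power calculations; Study design): 226 per group at 90% power; 267 per group at 80% power; significance level 0.05, sidedness not stated; drop-out 30%; 630 in total, 315 per arm. The drop-out arithmetic does not depend on sidedness.

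**1. Can 630 be reproduced?** The usual inflation is n / (1 − 0.30). A common but wrong shortcut is n × 1.30.

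| Required per arm | n / 0.70 | Total | n × 1.30 | Total |
|---|---|---|---|---|
| 226 | 322.9 → 323 | 646 | 293.8 → 294 | 588 |
| 267 | 381.4 → 382 | 764 | 347.1 → 348 | 696 |

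None of these is 630. The nearest is 646, and 630 is 2.5% below it (16/646). To cover both outcomes from the plan's own figures the total would be 764, so 630 is 134 short.

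**2. What 630 leaves.** 315 × 0.70 = 220.5 per arm (441 in total).

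- Against 267: 267 − 220.5 = 46.5 short, 46.5/267 = 17%.
- Against 226: 226 − 220.5 = 5.5 short, 5.5/226 = 2.4%.

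**3. Drop-out that 315 per arm can absorb.** For 267: 1 − 267/315 = 15.2%. For 226: 1 − 226/315 = 28.3%.

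**4. Power for suicidal ideation, taking 267 at face value.** If 267 gives 80% two-sided, the standardised effect at that size is 1.960 + 0.842 = 2.802. At 220.5 per arm, power = Φ(2.802 × √(220.5/267) − 1.960) = Φ(0.586) = 72%.

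**5. Power for the primary difference.** No SD is stated, so it is solved from 226 (two-sided, normal approximation): SD = 0.73 × √(226/2) / (1.960 + 1.282) = 2.39, a standardised difference of 0.305. At 220.5 per arm, power = Φ(3.242 × √(220.5/226) − 1.960) = 89%. A one-sided reading implies an SD of 2.65 and also gives 89%.

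**6. Power for the stated rates, 13% versus 8%.** Two-proportion normal approximation with pooled variance under the null; the pooled rate is 0.105.

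At 220.5 per arm the null standard error is √(2 × 0.105 × 0.895 / 220.5) = 0.0292, and the alternative standard error is √((0.13 × 0.87 + 0.08 × 0.92) / 220.5) = 0.0291. Two-sided power = Φ((0.05 − 1.960 × 0.0292) / 0.0291) = 40%.

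| Per arm | Two-sided | One-sided |
|---|---|---|
| 267 | 47% | 60% |
| 220.5 | 40% | 53% |

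The two-sided loss from 80% to 40% therefore splits in two. About 33 points (80% to 47%) arise because 267 does not follow from 13% versus 8%; the same method gives 589 per group two-sided, or 464 one-sided. About 7 points (47% to 40%) are due to drop-out.

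**The case against.** **The primary outcome is barely affected.** This stands. A gap of 5.5 per arm costs about one point of power. Even that is not certain at six months: the primary difference is powered at post-intervention, and the plan does not say when the 30% accrues. If 30% is the 12-month loss and the six-month loss is 28.3% or less, 226 is met. The Study objectives section also sets the primary comparison at 12 months, so this limits certainty without removing the gap. A reader might infer that the primary power claim collapses as the secondary one does; the figures do not support that.

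**The 89% depends on an unstated SD.** Also true. It takes 226 as correct and works back from it, so it must be labelled as an assumption.

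**Imputation makes good the loss.** The Statistical methods section plans intention-to-treat analysis with missing values filled from each participant's own responses, so it is observed data, not analysed participants, that fall short. But filling in values does not restore lost information, and the plan's own drop-out allowance treats it as lost. The Data collection section also names suicidal ideation only at follow-up, so an early drop-out may have no response of their own to draw on.

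**The 30% could be a slip for 15%.** Since 267/0.85 = 314.1, which rounds up to 315, a reader might infer that 15% was meant. No section says so. Restating drop-out as 15% would swap the trial's assumption for one chosen to fit 630, and would keep 267, which does not follow from 13% versus 8%.

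**Conclusion.** The inconsistency is real: 226, 267, 30% and 630 cannot all stand together with the claim of adequate power for both outcomes. The material failure is against 267: 17% too few with observed data, and power of about 72% rather than 80% even if 267 is accepted. The failure against 226 is marginal, about 89% rather than 90%, given the implied SD and 30% loss at the time of analysis.

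A reader might put the whole fall to about 40% power for 13% versus 8% down to drop-out. That would be wrong: at 267 per arm power is already only about 47% two-sided, so drop-out accounts for about 7 points and the rest belongs to the separate error in 267. The drop-out inconsistency holds whether or not 267 is corrected. The power figures rest on normal approximations; the one-sided alternative is given because sidedness is not stated.

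**What to change.** Keep 630 and the 30% assumption, and correct what is said to follow from them, in Same size and power calculations:

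1. State that about 220 per arm are expected to have observed data.
2. Restate power at that number: about 89% for the primary difference, with the SD of about 2.39 named as implied by 226 or replaced by a sourced value; and for 13% versus 8%, about 40% two-sided or about 53% one-sided, with the sidedness declared.
3. Remove or amend the closing statement that the sample has adequate power for both primary and secondary outcomes.

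The cost is a few sentences and a less favourable stated power, with no extra participants. Raising enrolment to 764 would restore only the plan's own 267 and may be hard to achieve. At the plan's 20 claims a day, and assuming 60 to 65 working days in three months (1,200 to 1,300 claims), 630 is already 48% to 53% of claimants before eligibility and consent; over 90 calendar days (1,800 claims) it is 35%. The Trial status section says that full enrolment had yet to start, so the text can be corrected beforehand.

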### Statistical methods

Intention-to-treat analyses are planned to compare the effectiveness of the Contact&Connect package of interventions on post-intervention. To account for the presence of missing data at the post-intervention and follow-up assessments, we plan to utilise imputation from the participants’ own responses either prior to and, if available, subsequent to drop-out to estimate likely values for missing variables. Simulation work suggests these two methods demonstrate greatest accuracy, least bias, and least reduction in dispersion as compared to other imputation methods [23].

The efficacy of this intervention on both the primary and secondary outcomes will be assessed using multivariate regression modelling. As we anticipate that some participants may become re-employed during the intervention or follow-up period, analyses will be adjusted for number of days reemployed during the intervention and follow-up period. Analyses will be undertaken in Stata for Windows, version 13 [13].

The intervention will also be evaluated qualitatively *post hoc* for appropriateness, ability to engage participants, and overall impact using a semi-structured interview with a random sub-sample of 20 participants. Interviews will be conducted over the phone within eight weeks of the conclusion of the intervention by trained researchers. Data from these interviews will be analysed thematically using NVivo for Windows, version 10 [24].

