### Intervention condition

Participants assigned to the intervention arm of this trial will receive a series of 12 informational and educational BCIs delivered to their smart phone over an intervention period of six months. Specific BCIs will target the specific outcomes of the project. Thus, separate BCIs will target knowledge about risk and protective factors for depression and suicide, the importance of social support through connections with friends, family, work colleagues, dispelling myths about mental health problems (in others and the self), and improving knowledge about help-seeking and communication.

Contact&Connect will be delivered to participants’ smart phones via rich text messages with embedded hyperlinks to microsites and other digital resources such as videos and digital wallet cards. These additional resources will provide additional information on stigma, mental health and help seeking, provide links to sources of help whilst encouraging the establishment and maintenance of long-term contact with others. BCIs will be delivered using Whispir^TM^ enterprise edition; an automated and programmable SMS message and communication management system. In addition to allowing multiple types of communication at once, this software will enable us to track participants’ engagement with various BCI materials.

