### Control condition

Participants randomised to the control condition will be allocated to a wait-list and will receive the intervention materials in full at the conclusion of the intervention period.

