### Data collection

All participants will complete a baseline electronic survey comprising information on sociodemographic information at the time of study enrolment, knowledge of depression symptoms, attitudes towards those with depression, and stigma, shame, self-blame or social inadequacy. Follow-up surveys will take place immediately post-intervention (six months), and then again at 12 months following enrolment to collect information on changes in knowledge of depression symptoms, attitudes towards those with depression, stigma, shame, self-blame, and social inadequacy and also to assess the impact of the intervention on suicidal ideation and depression symptomatology.

Primary outcome measures will include: scores on the attitudes, beliefs, and help-seeking inhibition subscales of the Depression Stigma Scale (DSS; [10]) and the shame, self-blame and social inadequacy subscales of the Self-Stigma of Depression Scale (SSDS; [16]), and levels of perceived social support from family and friends using the Multidimensional Scale of Perceived Social Support (MSPSS; [17]). Secondary outcomes will include: suicidal ideation as measured by scores on the suicidality subscale of the General Health Questionnarire-28 (GHQ-28; [18]) and depression symptomatology as measured by scores on the Center for Epidemiologic Studies Depression scale-Revised (CESD-R; [19]) and the depression subscale of the Brief Symptom Inventory (BSI; [20]).

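### Imputing missing outcomes from each participant's own earlier or later answers pulls the six-month effect towards zero and, in a wait-list design, can draw on controls' answers given after they received the package

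*Protocol article*

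**What the plan says.** The Statistical methods section of the protocol article announces intention-to-treat analyses and fixes the handling of missing data. "To account for the presence of missing data at the post-intervention and follow-up assessments", it will impute from participants' "own responses either prior to and, if available, subsequent to drop-out to estimate likely values for missing variables". It defends the choice by reference to a cited study: "Simulation work suggests these two methods demonstrate greatest accuracy, least bias, and least reduction in dispersion as compared to other imputation methods". Primary and secondary outcomes then "will be assessed using multivariate regression modelling". No multiple draws, pooling, likelihood-based handling or sensitivity analysis is mentioned.

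Three other sections bear on this:
- **Intervention condition:** the messages are "delivered to their smart phone over an intervention period of six months".
- **Control condition:** wait-list participants "will receive the intervention materials in full at the conclusion of the intervention period".
- **Data collection:** after the baseline survey, "Follow-up surveys will take place immediately post-intervention (six months), and then again at 12 months following enrolment".

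The sample-size section gives the expected amount of missing data: "Assuming 30 % drop-out, we therefore aim to recruit a total of 630 newly unemployed participants".

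**The concern.** With three survey occasions, a person's own answers offer little to impute from. A participant who leaves before six months and does not return has only a baseline score. Any value built from that score alone assumes that the person did not change, whichever arm they were in. If the package works, this mixes the real effect in those observed with an assumed zero effect in up to 30% of the sample.

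A participant who misses six months but answers at 12 months also has a later answer. For a control, that answer comes after the package was delivered, yet it would help to fill a score meant to describe an untreated person.

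At stake is the six-month comparison, the only follow-up comparison before controls receive the package. A true effect would be understated and its interval would often miss it. Under some patterns of loss, a false effect could also appear.

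**Working it through.** **Inputs from the article:** 315 per arm; 30% drop-out; 226 per group at the 0.05 level with 90% power; surveys at baseline, six and 12 months. The article gives no figure for the imputation itself, so there is none to reproduce.

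**Assumptions (not in the article):**
- Effect size. The article gives a difference of 0.73 without an SD. Solving the two-mean formula for 226 per group, two-sided, gives d = √[2(1.960 + 1.282)²/226] = 0.305 SD, which implies an SD of 0.73/0.305 = 2.39.
- Correlation between visits of 0.6, SD 1 at each visit, and loss completely at random.
- Own-response imputation for drop-outs means that the baseline score is carried to six months. Analysis is regression on arm and baseline.

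**1. Attenuation.** The share observed is 0.7, and imputed values carry no effect. Expected estimate = 0.7 × 0.305 + 0.3 × 0 = 0.2135 SD, a 30% reduction. This does not depend on the correlation.

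**2. Standard error and coverage.**
- Observed data only: n = 0.7 × 315 = 220.5 per arm; SE = √[2(1 − 0.6²)/220.5] = 0.076.
- Nobody missing: SE = √[2(1 − 0.6²)/315] = 0.064.
- Baseline carried forward: slope on baseline = 0.7 × 0.6 + 0.3 = 0.72. Residual variance = 0.7(1 + 0.72² − 2 × 0.72 × 0.6) + 0.3(1 − 0.72)² = 0.458 + 0.024 = 0.482. Mixing people with and without the effect in the intervention arm adds ½ × 0.21 × 0.305² = 0.010. SE = √(2 × 0.491/315) = 0.056.
- Bias/SE = 0.0915/0.056 = 1.63, so coverage is about Φ(1.96 − 1.63) = 0.63. Simulated trials gave an estimate of 0.21, SE 0.056 and coverage of 61–62%. Observed-data regression gave about 0.305, SE 0.076 and coverage of 95%. At correlations of 0.4 and 0.7 the simulated coverage was 73% and 54%.

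The model SE of 0.056 matches the simulated spread of the estimates (0.056–0.057). It is therefore correct for this estimator, and the poor coverage comes from bias. It is nevertheless below the 0.064 that would apply with no missing data, so it implies more information on the six-month effect than the trial would hold.

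**3. Type I error.** With no effect and a common drift D, the false difference is D × (loss in one arm − loss in the other). The drift adds to the residual variance, giving SE of about 0.058 in the two unequal-loss rows.

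| Drift | Loss by arm | False difference | Approximate rejection rate | Simulated |
|---|---|---|---|---|
| 0.5 SD | 35% vs 25% | 0.05 | Φ(−1.96 + 0.86) + Φ(−1.96 − 0.86) = 14% | 13–15% |
| 0.5 SD | 40% vs 20% | 0.10 | Φ(−1.96 + 1.72) + Φ(−1.96 − 1.72) = 41% | 38–41% |
| 0.5 SD | 30% vs 30% | 0 | 5% | 4.3% |
| none | 35% vs 25% | 0 | 5% | 4.8% |

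**4. Controls' 12-month answers.** Suppose a missing six-month score is the mean of baseline and 12 months, and the intervention-arm effect persists to 12 months. If controls have not caught up, imputed scores carry half the effect (0.1525). If they have caught up fully, imputed scores carry none.
- 20% drop-out plus 10% missing only six months: 0.2135 + 0.1 × 0.1525 = 0.229 without catch-up, 0.2135 with it.
- 25% plus 5%: 0.2135 + 0.05 × 0.1525 = 0.221 without, 0.2135 with.
- Extreme case, all 30% missing only six months: 0.2135 + 0.3 × 0.1525 = 0.259 without, 0.2135 with.

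**The case against.** The article names no algorithm. Carry-forward, averaging, and model-based imputation with a person's own scores as predictors all fit the wording, and the number of imputations and pooling rules are details that an article may leave to the analysis plan. This stands in part. Single imputation is an inference, but the likelier reading: values come from the person's own answers, two methods are named, they are judged on retained dispersion, and no pooling is mentioned.

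In the only loss scenario that the article states, 30% with no difference between arms, the test remains valid, the bias is towards no effect, and power hardly changes (96.8% against 97.6% with observed data in simulation). This stands. A reader might infer that the method inflates type I error in general or that the software would miscalculate the SE. The results support neither: inflation needs drift and unequal loss together, and neither figure is in the article. With 32% vs 28% loss and 0.5 SD drift the error is only 6.5%.

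A reader might also take the justification as an admission of lost dispersion. It claims the least reduction among the methods compared, and the cited study is not at hand to check. Even a sound general ranking would not address the use of controls' answers after crossover.

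The good behaviour of observed-data regression here follows from simulating random loss. The article states no mechanism for missingness.

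**Conclusion.** The concern holds in a limited form. The stated method is poor for this design because, where only baseline is available, it assumes no change. On the single-imputation reading, with 0.305 SD as the true effect, correlation 0.6 and 30% random loss in each arm, the six-month estimate shrinks to about 0.21 SD and coverage falls to about 61–62%. The 30% attenuation holds at any correlation; the coverage varies with it.

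Type I error stays near 5% with equal loss or with no common drift. The figures of about 13% and 40% require an assumed 0.5 SD drift together with 35% vs 25% or 40% vs 20% loss. Both conditions are conceivable, since the Discussion links re-employment to better mental health and participants know their allocation, but the article quantifies neither.

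The crossover route follows directly from the Intervention condition, Control condition and Data collection sections and needs no assumed parameter to exist. It is secondary in size. It affects only controls who miss six months and answer at 12, and its effect depends on how many there are and how far they catch up. It would be tempting to attribute a fall from 0.305 to 0.21 SD to crossover alone. That requires all 30% to miss only six months, their scores to be filled wholly from 12 months, and treated controls to catch up fully, which the documents do not support.

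**What to change.** Before analysis, replace the primary missing-data method with one of two options:
- a likelihood-based mixed model for repeated measures with arm, time, arm-by-time and baseline; or
- multiple imputation carried out separately by arm, combined with Rubin's rules.

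Both rest on missing at random, which should be stated. Both are available in the Stata 13 already planned. State that control 12-month values will not be substituted for missing six-month values. Keep own-response imputation as a sensitivity analysis, with its exact rule written down, and add a delta-adjusted analysis to test departures from missing at random.

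The cost is revised analysis wording, modest programming and wider confidence intervals. Recruitment, survey schedule and participant burden are unchanged.

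### The only covariate stated for the outcome regression is days re-employed, which arises after randomisation; the baseline stigma scores, collected from everyone, should be named in its place.

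*Protocol article*

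**What the plan says.** Protocol article, Statistical methods: "The efficacy of this intervention on both the primary and secondary outcomes will be assessed using multivariate regression modelling". The section expects some participants to find work during the trial, and so states that "analyses will be adjusted for number of days reemployed during the intervention and follow-up period". No other covariate is named anywhere in the article. The Discussion repeats that re-employment will be accounted for, but there limits it to the six-month intervention period.

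Protocol article, Data collection: the baseline survey, completed by all participants, covers "knowledge of depression symptoms, attitudes towards those with depression, and stigma, shame, self-blame or social inadequacy". The primary outcomes include "scores on the attitudes, beliefs, and help-seeking inhibition subscales of the Depression Stigma Scale" (DSS), the shame, self-blame and social inadequacy subscales of the Self-Stigma of Depression Scale (SSDS), and perceived social support (MSPSS). On later surveys: "Follow-up surveys will take place immediately post-intervention (six months), and then again at 12 months following enrolment to collect information on changes".

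Protocol article, Same size and power calculations: the primary calculation assumes "a difference of 0.73 in beliefs about depression treatment between the intervention and control groups at post-intervention" and concludes that "a minimum of 226 participants per group will be required to detect this difference at the nominal 0.05 significance level" with 90% power. Drop-out is taken as 30% and total recruitment as 630.

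**The concern.** There are two linked problems, and the first carries more weight.

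1. **The stated covariate is a post-randomisation variable.** A package that aims to change help-seeking, shame and social connection could plausibly change how soon a man returns to work. The article itself links re-employment to better mental health. Re-employment may therefore lie on the path from intervention to outcome. Conditioning on it can remove part of the effect, and can introduce bias through anything that drives both re-employment and the outcome. The result is then no longer the plain effect of being assigned to the intervention, which is what an intention-to-treat analysis is for.

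2. **The covariate that would help is not stated.** The baseline value of the same scale is usually among the best predictors of a follow-up score. It cannot be affected by allocation. Randomisation is simple, with no stratification described, so the design itself does not balance baseline stigma. Naming the baseline score would narrow the interval at no data cost.

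**Working it through.** **Inputs from the article:** difference 0.73; 226 per group; 90% power; significance level 0.05; drop-out 30%; 315 per arm.

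**Assumed, because not given:** a two-sided test; the outcome SD, back-solved below; the correlation r between baseline and follow-up scores, shown over a range; and a baseline value for the powered beliefs outcome.

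**Step 1. The article's own figure.** No SD is given, so 226 cannot be reproduced independently. It can only be inverted:

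SD = 0.73 / [(1.960 + 1.282) × √(2/226)] = 0.73 / 0.305 = 2.394.

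That is a standardised difference of 0.305. If the test were one-sided, the implied SD would be 2.652.

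**Step 2. Power as designed, without baseline.** Completers per arm: 315 × 0.7 = 220.5, taken as 220.

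Power = Φ(0.73 / [2.394 × √(2/220)] − 1.960) = Φ(3.198 − 1.960) = 0.892.

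**Step 3. Power with baseline.** Adjusting for a baseline score with correlation r multiplies the residual variance by 1 − r², so the residual SD is 2.394 × √(1 − r²). The equivalent unadjusted number per arm is 220 / (1 − r²).

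| Assumed r | Variance factor | Residual SD | Power at 220 per arm | Equivalent unadjusted n per arm | n per arm for 90% power |
|---|---|---|---|---|---|
| 0 | 1.00 | 2.394 | 89.2% | 220 | 226 |
| 0.3 | 0.91 | 2.284 | 91.8% | 242 | 206 |
| 0.5 | 0.75 | 2.073 | 95.8% | 293 | 170 |
| 0.6 | 0.64 | 1.915 | 97.9% | 344 | 145 |

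The variance factor does not depend on the back-solved SD; the power figures do.

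**Step 4. Comparison with the drop-out loss.** Drop-out takes 315 per arm to about 220, a factor of 0.70. Recovering that requires 1 − r² < 0.70, so r² > 0.30 and r above about 0.55. At r = 0.5 the equivalent is 293, still below 315; at r = 0.6 it is 344.

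**Step 5. Chance imbalance.** With 315 per arm, the standard error of a baseline difference is √(2/315) = 0.080 SD, giving a 95% range of about ±0.16 SD. At r = 0.5 this moves an unadjusted difference by up to about 0.16 × 0.5 = 0.08 SD, roughly a quarter of the 0.305 SD target. This is not a further gain on top of Step 3: it is the same variance seen another way.

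**Step 6. Which outcomes have a baseline value.** Data collection lists domains at baseline, not instruments. Attitudes, stigma, shame, self-blame and social inadequacy are there. DSS beliefs and help-seeking inhibition are not listed by name. MSPSS, GHQ-28, CESD-R and the BSI depression subscale are not listed at all.

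The bias from adjusting for re-employment cannot be sized: the article gives no effect of the intervention on re-employment and no association with these scales in this population.

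**The case against.** The strongest objection is that silence is being read as a decision. The article calls the model a multivariate regression, adds one covariate for a stated reason, and gives no closed list. A condensed article commonly leaves the covariate list to a fuller protocol or analysis plan. The text even points towards some use of baseline: follow-up surveys collect changes, and the mediation objective concerns changes in attitudes and beliefs. **This stands.** A reader might infer that the plan excludes the baseline scores and knowingly gives up precision; the article does not say so. What survives is that the covariate it does commit to is the post-randomisation one.

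Other points on that side:

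- **No lack of validity or power follows from the absence of baseline.** An unadjusted randomised comparison is unbiased, and power is about 89% against a 90% target. This stands. A reader might infer that simple randomisation biases the result or that the trial is underpowered on this outcome; neither is supported.
- **The size rests on inputs that the article does not give.** This stands. If the 0.73, or the SD behind 226, came from a change-score or baseline-adjusted analysis, part of the gain is already counted. The 0.73 concerns beliefs about treatment and is not shown to be on the DSS or SSDS metric. The calculation counts completers, whereas the plan imputes missing values.
- **Re-employment was chosen deliberately.** The Discussion explains it as protection against dilution. That is a fair reason to examine re-employment, but not to condition the main intention-to-treat estimate on it. If the intervention has no effect on re-employment, the adjustment does little harm, but the article cannot know that in advance.

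**Conclusion.** The point holds in a limited form. The article commits its outcome regression to a covariate that arises after randomisation and could be affected by the intervention. It states no baseline covariate, although baseline values for most of the stigma domains exist for everyone.

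The benefit of adding baseline is one of precision. At 220 completers per arm, power rises from about 89% to 92%, 96% and 98% for r = 0.3, 0.5 and 0.6. These figures assume a two-sided test, an SD of 2.39 inverted from the article's own sample size, and an unadjusted basis for that sample size. The gain is modest at r = 0.3. A reader might infer that a moderate correlation more than makes good the drop-out loss; that is true only above about r = 0.55. Nor do the documents support extending the gain to every primary and secondary outcome, since social support and the secondary scales are not listed at baseline.

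The case for removing days re-employed from the main model rests on principle, and its size is unknown.

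**What to change.** In Statistical methods, replace the re-employment adjustment in the primary model. For each DSS and SSDS subscale with a baseline value, specify the follow-up score regressed on arm plus the baseline score of the same subscale, at six months and at 12 months, since the primary objective covers both. Confirm which subscales the baseline survey contains, in particular DSS beliefs and help-seeking inhibition. Apply the same model to MSPSS and the secondary scales only if they are also collected at baseline.

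Re-employment may stay as a sensitivity or descriptive analysis, with its time window made the same in Statistical methods and in the Discussion.

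The cost is a sentence or two of text. No new data are needed for subscales already measured at baseline, and the recruitment target need not change on account of this point.
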